# A prospective, single-centre, randomised study evaluating the clinical, imaging and immunological depth of remission achieved by very early versus delayed Etanercept in patients with Rheumatoid Arthritis (VEDERA)

**DOI:** 10.1186/s12891-016-0915-0

**Published:** 2016-02-05

**Keywords:** Rheumatoid arthritis, Disease modifying anti-rheumatic drug, Etanercept, Treat to target, Remission, Clinical efficacy, MRI synovitis score, Molecular predictors of response

## Abstract

**Background:**

Rheumatoid arthritis (RA) is a chronic inflammatory arthritis, with significant impact on quality of life and functional status. Whilst biologic disease modifying anti-rheumatic drugs (bDMARD) such as tumour necrosis factor-inhibitor (TNFi) agents have revolutionised outcomes in RA, early diagnosis with immediate conventional therapy, titrated in a treat to target approach is also associated with high remission rates. The main aim of the VEDERA study (Very Early versus Delayed Etanercept in Rheumatoid Arthritis) is to assess the depth of remission, sustainability of remission and immunological normalisation induced by very early TNFi with etanercept (ETN) or standard of care +/- delayed ETN.

**Methods/Design:**

VEDERA is a pragmatic, phase IV single-centre open-label randomised superiority trial of 120 patients with early, treatment-naive RA. Patients will be randomised 1:1 to first-line ETN and methotrexate (MTX) or MTX with additional synthetic disease modifying anti-rheumatic drugs (sDMARDs) according to a treat to target (TT) protocol with further step up to ETN and MTX after 24 weeks if remission is not achieved. Participants will have regular disease activity assessments and imaging evaluation including musculoskeletal ultrasound and MRI. The main objective of this study is to assess the proportion of patients with early RA that achieve clinical remission at 48 weeks, following either treatment strategy. In addition, the participants are invited to take part in a cardio-vascular sub-study (Coronary Artery Disease in RA, CADERA), which aims to identify the incidence of cardiovascular abnormalities in early RA.

**Discussion:**

The hypothesis underlining this study is that very early treatment with first-line ETN increases the proportion of patients with rheumatoid arthritis achieving clinical remission, in comparison to conventional therapy.

**Trial registration:**

NCT02433184, 23/04/2015

## Background

Rheumatoid arthritis (RA) is a chronic inflammatory arthritis, characterised by symmetrical, often erosive, inflammatory polyarthritis of the small and medium sized joints, which can lead to significant disability and decreased function [1]. The overall burden of disease however extends beyond the joints to include wide-ranging extra-articular manifestations and comorbidities [2].

The fundamental paradigm in the management of RA is that early, effective suppression of synovitis by early diagnosis and immediate initiation of disease modifying anti rheumatic drug (DMARD) therapy is associated with improved outcomes. Guidelines recommend synthetic DMARD (sDMARD) as a first line therapy with step-up to biological DMARD (bDMARD) treatment in the presence of continued disease activity. Internationally agreed guidelines recommend a treat to target (TT) approach, a concept established for the management of pathologies such as arterial hypertension and diabetes [3]. In RA, TT implies frequent monitoring using a composite disease activity measure such as the disease activity score-28 joint (DAS28) and escalation of therapy according to a pre-defined target of remission or at least low disease activity (LDA) [4, 5]. Tight control of disease activity with intensive treatment, either step-up [6] or parallel [7, 8] in early RA is associated with an improvement in medium and long term outcomes.

The introduction of bDMARDs has provided highly effective therapy with which to achieve effective disease control [9–11]. There are currently five licensed tumour-necrosis factor-inhibitor (TNFi) therapies, the first bDMARDs to be approved for use, of which etanercept (ETN) is a recombinant TNF receptor fused to a human Fc molecule forming a bivalent TNF binding agent. ETN reduces inflammation, improves functional status and quality of life and inhibits radiographic progression [12, 13]. As with other TNFi, ETN is recommended following MTX-inadequate response [14], and in the UK after failure of at least two sDMARDs (of which one should be MTX) [15].

Recent studies including COMET [16], ASPIRE [17] and OPTIMA [18], suggest that TNFi therapy in the early phase of the disease, prior to failure of sDMARDs, offers improved rates of response and inhibition of radiographic progression in comparison to sDMARD. Sub-analysis of the COMET study shows that patients receiving very early treatment with ETN and methotrexate (within the first 4 months of disease) achieve greater rates of remission than those with longer disease [19]. Furthermore, studies suggest that when commenced early, TNFi may offer a greater depth of remission that is more likely to be sustained after drug withdrawal [20]. In recent years, increasing consideration has been given to the ‘window of opportunity’ concept: a phase in early disease in which it may be possible to alter the pathogenic course of the disease [21]. However, not all studies demonstrate the superiority of TNFi when compared to TT regimen in early disease; in a group of DMARD-naive early RA patients, no statistically significant differences were found between patients receiving MTX and intravenous steroids, followed by TT regimen and combination therapy with MTX and infliximab [22]. There is thus, continued debate on how best to apply TNFi therapies in order to obtain the maximal benefits to the patient whilst considering socio- and health-economic costs. In addition, increasing research is aimed at identifying predictors of response. This includes use of TNFi within a TT strategy [17, 18], and for remission [23].

An additional challenge is the assessment of therapeutic response. Whilst clinical scores such as DAS28 form the basis of evaluation, it is accepted that these may be insensitive [24]; imaging modalities such as power Doppler (PD) ultrasound (US) and dynamic magnetic resonance imaging (MRI) enable more accurate assessment of inflammation as well as providing insights into the pathobiology of disease [25].

## Methods/Design

### Aims and objectives

The main aim of the VEDERA study (Very Early versus Delayed ETN in Rheumatoid Arthritis) is to evaluate the depth of remission, sustainability of remission and immunological normalisation induced by very early TNFi or the current standard of care (with or without delayed TNFi if required), in patients with early, treatment-naive RA.

#### Research hypothesis

Very early treatment with first-line ETN increases the proportion of patients with rheumatoid arthritis achieving clinical remission, in comparison to conventional therapy.

#### Primary objective

The primary objective of this study is to assess the proportion of patients with early, treatment-naive RA that achieve clinical remission at 48 weeks following first-line ETN and MTX (‘very early ETN’) or MTX with additional sDMARDs and step up to ETN and MTX at 24 weeks, as required according to a TT protocol aiming for remission (‘delayed ETN’).

#### Secondary objectives

To assess the change in MRI synovitis between baseline and 48 weeks following very early ETN or MTX-TT regimen +/- delayed ETN.To evaluate other clinical efficacy endpoints at weeks 12, 24, 48 and 96 including:✓ Disease activity score-44 joint (DAS44) remission (DAS44 < 1.6), simplified disease activity index (SDAI), clinical disease activity index (CDAI), European League Against Rheumatism (EULAR) response criteria, American College of Rheumatology (ACR) response criteria.✓ Cumulative steroid dose.To evaluate patient-reported outcomes at weeks 12, 24, 48 and 96 including:✓ Physical function, assessed by the Health Assessment Questionnaire (HAQ), including normalisation of HAQ.✓ Quality of life scores assessed by RA Quality of Life (RA-QoL) and Euro QoL Five Dimensions (EQ-5D) questionnaires.✓ Work instability, assessed by RA Work Instability Score (RA-WIS) questionnaire.To evaluate imaging predictors of remission and sustained remission using:✓ High-resolution ultrasound (HRUS) at weeks 0, 12, 24 and 48 measuring grey scale (GS), PD and presence or absence of erosions.✓ Magnetic Resonance Imaging (MRI) at weeks 0, 12, 24 and 96 measuring synovitis and erosion scores.To evaluate other radiographic outcomes including:✓ Joint damage assessed by modified Sharp score of X-rays of hands and feet at weeks 48 and 96.

#### Exploratory objectives

To investigate immunological abnormalities and cellular/molecular predictors of response to the two therapeutic strategies using:✓ Blood, sampled at baseline and weeks 12, 24, 36, 48 and 96.✓ Synovial tissue (optional), biopsied from a target joint at baseline and 24 weeks; at 48 weeks for treatment arm 2 who have switched to ETN and at time of flare.

### Study design

The VEDERA study is a phase IV single-centre open-label randomised trial of 120 patients with early, treatment-naive RA. Patients will be randomised 1:1 to first-line ETN and MTX or MTX with additional sDMARDs and step up to ETN and MTX after 24 weeks as required according to a TT protocol aiming for remission.

The randomised trial duration is 48 weeks after which ETN will be stopped and patients will continue for a 48-week observational period during which DMARDs will be used as per standard care, in accordance with national guidelines.

### Patient eligibility

The target population are males and females, aged between 18 and 80 years, fulfilling the 2010 American College of Rheumatology/European League against Rheumatism (ACR/EULAR) RA classification criteria, who have not yet received DMARD therapy, with a maximum symptom duration of 12 months. Other criteria for inclusion are: patients with active RA at baseline (clinical evidence of synovitis and DAS28-ESR > 3.2) and positive anti-citrullinated peptide antibody (ACPA) or rheumatoid factor (RF) status. In the absence of RF and ACPA antibodies, patients are eligible for the study if they have evidence of power Doppler, a good indicator of active inflammatory pathology and predictor of structural damage. Power Doppler grade ≥1 in at least 1 joint on hand ultrasound is required (Table 1).

**Table 1 Tab1:** Eligibility criteria for randomisation into VEDERA trial

Inclusion Criteria
• Male and female patients aged between 18 and 80 years.
• Diagnosis of rheumatoid arthritis (new 2010 ACR/EULAR RA classification criteria).
• Symptom onset within the preceding 12 months.
• Patients with active RA at baseline: clinical evidence of synovitis (or imaging-evidence of synovitis in cases of uncertainty/subclinical disease) in hand and/or wrist joints evaluable by ultrasound and MRI, and DAS28-ESR > 3.2.
• Seropositivity for anti-citrullinated peptide antibody (ACPA) and/or rheumatoid factor. If ACPA and rheumatoid factor are both negative, presence of power Doppler (grade 1 or higher) in at least 1 joint on hand ultrasound is required.
• DMARD-naive (with the exception of previous exposure to hydroxycholorquine for an indication other than RA).
• All male and female subjects biologically capable of having children must agree to use a reliable method of contraception for the duration of the study and 24 weeks after the end of the study period. Acceptable methods of contraception are surgical sterilisation, oral, implantable or injectable hormonal methods, intrauterine devices or barrier contraceptives.
Exclusion Criteria
• Previous treatment with DMARDs for the management of RA.
• Intramuscular or intra-articular (of non-target joint) corticosteroid within 28 days of the screening visit; intra-articular steroid of the chosen target joint within 12 weeks of screening.
• Oral steroid of greater than 10mg prednisolone daily, or change in oral steroid dose within 28 days of study drug initiation at the baseline visit.
• Use (including use as required) of more than one NSAID, change in NSAID or change in dose of NSAID within 28 days of the baseline visit.
• Contraindications to MRI (e.g. pacemaker) or unable or unwilling to attend for all imaging assessments. In patients with previous penetrating trauma to the eye, or patients at high risk of previous metal foreign body injury to the eye (e.g. welding), skull x-ray will be performed; these patients may be included in the absence of residual metal fragments on x-ray.
• Pregnancy or breastfeeding.
• Other contraindications to TNFi as determined by local prescribing guidelines and physician discretion, including: active infection, open leg ulcers, previously infected prosthetic joint (unless completely removed), septic arthritis in last year, HIV, Hepatitis B or Hepatitis C carriers, previous malignancy within 10 years (except basal cell carcinoma), severe heart failure (New York Heart Association grade 3 or more), any history of demyelinating disease, uncontrolled diabetes, pulmonary fibrosis, bronchiectasis, previous PUVA therapy (of >1000 Joules), history of TB or evidence of latent TB on chest x-ray/TB testing (in the latter event, a patient may be included if treated with isoniazid and pyridoxine one month before starting the study and for a further 6 months whilst on study treatments).

### Recruitment

Participants will be recruited from the rheumatology clinics based within Leeds Teaching Hospitals NHS Trust. The recruitment period is expected to last up to 36 months. All patients in the VEDERA study will be invited to participate in CADERA, the cardiovascular sub-study.

### Screening

Following written informed consent and prior to any trial related procedures, participants will be registered and undergo a screening assessment that should occur no more than four weeks prior to the baseline assessments, to determine eligibility for the study.

### Randomisation

Once eligibility is confirmed and all relevant procedures have been completed, participants will be block randomised 1:1 to one of the following two treatment groups (Fig. 1):Treatment Arm 1 or ‘very early ETN’ will receive ETN and MTX combination therapy administered for a total duration of 48 weeks.Treatment Arm 2 or ‘delayed ETN’ will receive initial MTX monotherapy with adoption of a TT protocol (standard care involving monthly DAS28-ESR assessment with escalation to combination sDMARD therapy if not achieving LDA at, or after, 8 weeks) and step-up to ETN and MTX at 24 weeks if failing to achieve clinical remission.

**Fig. 1 Fig1:**
[figure not shown]
Schematic of the trial design. DMARD disease modifying antirheumatic drugs, ETN etanercept, HCQ hydroxychloroquine, LDA low disease activity, MTX methotrexate, NICE National Institute of Clinical Excellence, RA rheumatoid arthritis, SSZ sulfasalazine, TT treat to target

### Trial intervention

#### Treatment arm one

For treatment arm one (Table 2), ETN will be administered subcutaneously up to week 48 (except in the case of intolerance or subject withdrawal) at a dose of 50 mg weekly. MTX will be administered orally at a starting dose of 15 mg weekly, increasing to 20mg and 25mg weekly at weeks 4 and 8 respectively. Patients that are clear non-responders or intolerant to ETN and/or MTX will be managed according to physician discretion (withdrawing these study treatments if appropriate).

**Table 2 Tab2:** Treatment arm scheme

Arm 1	Dosage form	Dosage regimen	Duration
*ETN*	Subcutaneous	50mg weekly	Up to week 48 unless non-response or intolerance.
*MTX*	2.5/10mg tablets (or s.c. if oral not tolerated)	Weeks 0-4: 15 mg weekly Week 4: 20 mg weekly Week 8 onwards: 25 mg weekly	For duration of study (unless intolerance: aim for maximum tolerated dose)
*Folic Acid*	5mg tablets	5mg, six days per week (not day of MTX)	For duration of study (if receiving MTX)
Arm 2			
*MTX*	2.5/10mg tablets (or s.c. if oral not tolerated)	Weeks 0-2: 15 mg weekly Week 2 onwards: 25 mg weekly	For duration of study (unless intolerance, aim for maximum tolerated dose)
*Folic Acid*	5mg tablets	5mg six days per week (not day of MTX)	For duration of study (if receiving MTX)
*SSZ*	500 mg tablets	1 g twice a day	At/after week 8 if not achieving low disease activity (DAS28ESR > 3.2). Discontinuation if ETN is started at week 24.
*HCQ*	200mg tablets	200mg tablets	At/after week 8 if not achieving low disease activity (DAS28ESR > 3.2). Discontinuation if ETN is started at week 24.
*ETN*	Subcutaneous	50mg weekly	At week 24 to week 48 if not achieving remission (DAS28ESR ≥ 2.6) Thereafter continuation will be determined by physician judgement/according to national guidelines.

*ETN* Etanercept, *MTX* Methotrexate, *SSZ* Sulfasalazine, *HCQ* Hydroxychloroquine

#### Treatment arm two

In treatment arm two (Table 2), MTX will be administered orally at a starting dose of 15 mg and will be increased to 25mg weekly at 2 weeks. Subcutaneous MTX may be administered if intolerance to oral MTX is observed. If at weeks 8, 12, 16 or 20, the subject fails to achieve LDA (defined as DAS28-ESR ≤ 3.2), sulfasalazine (SSZ) and hydroxychloroquine (HCQ) will be added to MTX. SSZ will be administered orally at a dose of 1g twice daily (or at the maximum tolerated dose). HCQ will be administered at a dose of 200mg daily. At 24 weeks, if a subject fails to achieve clinical remission, ETN will be added to MTX, and SSZ and HCQ will be discontinued (if applicable).

#### Treatment arms 1 and 2

Oral folic acid will be administered at a dose of 5mg daily (except on the day of MTX) to subjects in both treatment arms.

ETN will be discontinued in both arms at the primary endpoint (48 weeks), with the exception of those patients who are eligible to continue according to local prescribing guidelines (NICE guidelines) [15].

A single non-steroidal anti-inflammatory drug (NSAID) is permitted providing the dose has been unchanged for at least 28 days prior to study drug initiation at baseline. The NSAID or NSAID dose may be changed during the time course of the study if indicated.

Oral prednisolone is permitted at doses up to and including 10mg prednisolone daily if the dose has been stable for at least 28 days prior to study drug initiation at baseline. The steroid dose may be reduced throughout the study.

Intramuscular steroid may be administered as per the study treatment protocol for each arm with all patients receiving 120mg intramuscular methylprednisolone (unless contraindicated or not tolerated) at baseline and at the following time-points according to treatment arm and disease activity:Week 12: both treatment arms, if DAS28-ESR > 3.2Week 24: treatment arm 1, if DAS28-ESR ≥ 2.6 (treatment arm 2 switch to ETN+/-MTX if DAS28-ESR ≥ 2.6)Week 36:✓ Treatment arm 1, if DAS28-ESR≥2.6✓ Treatment arm 2, sDMARDs (MTX +/-SSZ +/-HCQ), if DAS28-ESR≥2.6✓ Treatment arm 2, switched to ETN+/-MTX, if DAS28-ESR>3.2Up to the primary endpoint (week 48), for a patient with active disease who is judged by the physician to be in need of rescue therapy, and for whom it is considered to be unethical to wait until the 12, 24 and 36 week time points above, 120mg methylprednisolone may be administered.

At and/or after the primary endpoint (week 48) intramuscular or intra-articular steroids are permitted according to physician judgment, unless a clinical or imaging assessment is scheduled within the following 6 weeks.

Alternative DMARDs, other than study treatments, are permitted if clinically indicated in a subject judged by the physician to be a non-responder (primary or secondary non-responder) or intolerant to ETN.

#### Prohibited medications

Steroids are prohibited prior to week 48, with the exception of:Patients receiving ≤10mg prednisolone daily with a stable dose for at least 28 days prior to study drug initiation at baseline.Patients receiving prednisolone for an indication other than arthritis, for example asthma or chronic obstructive pulmonary disease (up to a maximum total oral dose of 250mg, and a maximum duration of 14 days).Intramuscular steroid as per the study treatment protocol for each arm.120mg methylprednisolone administered as rescue therapy (see above).

In the unavoidable instance of a subject receiving corticosteroid within a significant time window prior to a clinical +/- imaging joint assessment the assessment will not be performed. A significant time window is defined as follows: intramuscular corticosteroid within 4 weeks or oral prednisolone within 7 days of the assessment, except patients on stable prednisolone ≤10mg.

At or after week 48, intramuscular or intra-articular steroids are prohibited within 6 weeks of a scheduled clinical or imaging assessment.

Other prohibited medications are any alkylating agents (e.g. cyclophosphamide, chlorambucil), any experimental drugs and immunisations with live vaccines.

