### Methods of assessment

#### Clinical efficacy

Clinical efficacy and remission will be assessed by the following measures, with joint examinations performed by the same blinded assessor.

*DAS44 and DAS28*, based on the evaluation of four variables: tender joint assessment (Ritchie Articular Index, RAI, and 28 joint count respectively), number of swollen joints (out of 44 and 28, respectively), erythrocyte sedimentation rate (ESR; mm/h) and patient’s global assessment of arthritis, as assessed by a 100 mm visual analogue scale (VAS). These will be performed at each visit for both treatment arms. The scores will be calculated using the following formulae: DAS28 = 0.56*sqrt (tender28) + 0.28*sqrt(swollen28) + 0.70*ln(ESR) + 0.014*VAS; DAS 44 = 0.54*sqrt(RAI) + 0.065*(swollen 44) + 0.33*ln(ESR) + 0.0072*VAS. Remission thresholds for DAS44 and DAS28 are <1.6 and <2.6 respectively [26].

*CDAI* is the sum of four variables: number of tender and swollen joints (out of 28), the investigator’s global assessment of disease activity and the patient’s global assessment of arthritis assessed by VAS (cm). The threshold for CDAI remission is <2.8 [27].

*SDAI* is the CDAI plus CRP (mg/dL). The threshold for SDAI remission is <3.3 [28].

*EULAR response criteria* classify patients as good, moderate or non-responders based on a combination of the actual DAS and change from previous DAS [29].

*ACR response* measures 20 % (ACR20), 50 % (ACR50) or 70 % (ACR70) improvement in tender and swollen joint counts and in at least three of the following parameters: patient global assessment, physician global assessment, pain, disability and acute phase reactant (ESR or CRP) [30].

*The physician global assessment* of rheumatoid disease activity should be completed before the patient’s global assessment is received. The investigator will mark their assessment on a 100 mm visual analogue scale (VAS): the left end corresponds to none (0) and the right end to extremely active (100).

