### Statistical considerations

#### Sample size

Clinical remission (DAS28 remission) forms the basis of the primary outcome. The COMET study, reported remission rates in patients with very early RA (less than 4 months since diagnosis) treated with both ETN and MTX or MTX monotherapy of 70 % versus 35 % respectively. In patients with disease duration of less than 2 years but greater than 4 months, treatment with ETN and MTX was associated with 48 % remission rate. In the COMET study patients in the very early RA group were recruited within 4 months of RA diagnosis, using ACR 1987 criteria. In contrast, VEDERA will recruit patients within 12 months of symptom onset. Whilst all patients will meet RA criteria at the point of recruitment, ACR/EULAR 2010 criteria are being used, which identify patients at an earlier stage of the disease course than the 1987 criteria, and patients can potentially be recruited concurrently with diagnosis. It is likely that patients recruited to VEDERA will be at a similar stage in their disease course to the patients in the very early RA group in COMET, potentially an even earlier stage.

To account for the possibility that the interval between the treatment groups may not be as large as that seen in COMET a 30 % difference has been used as a basis for the sample size calculation. Assuming therefore that patients in treatment arm 1 are likely to achieve up to 70 % remission, and treatment arm 2 approximately 40 % remission; for 80 % power at the 5 % significance level and allowing for a 10 % dropout rate, at least 49 patients per arm will be required. Increasing this to 60 per arm would allow for a subgroup analysis of treatment arm 2 patients that proceed to require delayed ETN and MTX to be compared with treatment arm 1 and indeed those in arm 2 that stay on conventional therapy. This is an exploratory analysis; we estimate that 50 % of treatment arm 2 patients will require delayed ETN and MTX. With roughly 30 patients in each subgroup of treatment arm 2 we will obtain sufficiently accurate estimates of remission rates.

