##### Missing data

For response variables (including the primary outcome) patients who discontinue study medication for lack of efficacy will be considered non-responders from that point forward. In all other instances, missing data will be addressed using multiple imputation. This technique assumes the data are missing at random; additional sensitivity analyses will include complete case analysis, best case/worst case single imputation, and imputation of a range of values to test the possible implications for the study conclusions if data are missing not at random.

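### Rescue steroid for active RA in the 4 weeks before week 48 removes the primary joint count, and remission status is then imputed as missing at random instead of being classified

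*Protocol article*

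**What the plan says.** The point arises from several sections of the protocol article read together.

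- **Primary outcome (Sample size):** "Clinical remission (DAS28 remission) forms the basis of the primary outcome". It is assessed at week 48, with remission set at DAS28 below 2.6 (Clinical efficacy). DAS28 is "based on the evaluation of four variables: tender joint assessment", swollen joint count, ESR and patient global VAS.
- **Rescue (Treatment arms 1 and 2):** up to week 48, 120 mg methylprednisolone may be given "for a patient with active disease who is judged by the physician to be in need of rescue therapy" when waiting is considered unethical. Prohibited medications lists this as a permitted exception to the steroid ban.
- **Assessment window (Prohibited medications):** for a subject "receiving corticosteroid within a significant time window prior to a clinical +/- imaging joint assessment the assessment will not be performed". The window is "intramuscular corticosteroid within 4 weeks or oral prednisolone within 7 days of the assessment", with an exception for stable low-dose prednisolone. No rescheduled assessment is described.
- **Missing data:** "patients who discontinue study medication for lack of efficacy will be considered non-responders from that point forward". Then: "In all other instances, missing data will be addressed using multiple imputation. This technique assumes the data are missing at random". The section states that its responder rule includes the primary outcome. It adds complete-case, best/worst-case and missing-not-at-random sensitivity analyses.

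**The concern.** The plan creates a gap in the primary outcome because the patient's disease was active shortly before the endpoint, then fills it as though, given the data in the imputation model, the gap said nothing about the outcome. A patient judged to need rescue in week 45 who stays on study drug can be imputed as in remission at week 48. A patient who stopped study drug for lack of efficacy is a non-responder. The two have similar clinical histories but are handled by opposite rules.

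What is at stake is the week-48 remission rate in each arm and the difference between arms. Rescue is a physician's judgement in an open-label trial, so equal use in the two arms cannot be assumed.

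**Working it through.** **1. Does the chain close?**

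| Step | Source | Result |
|---|---|---|
| Rescue possible in weeks 44-48 | Treatment arms 1 and 2 | Yes, up to week 48 |
| Scheduled intramuscular doses in that window | Same section | None; the last is week 36 |
| Week-48 joint assessment after such rescue | Prohibited medications | Not performed |
| DAS28 without joint counts | Clinical efficacy | Cannot be calculated |
| Non-responder rule | Missing data | Applies only on discontinuation for lack of efficacy |
| All other missing outcomes | Missing data | Multiple imputation, missing at random |
| Last scheduled joint assessment before week 48 | Study schedule; Table 3 | Week 36 |

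The chain closes for rescued patients who remain on study medication. A flare after week 36 falls after the last complete DAS28 available to the imputation.

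**2. Design rates.** The protocol has no figure for late rescue, so the only planning inputs are 70 % versus 40 % remission and 60 per arm. The stated 49 per arm reproduces with the pooled variance under both hypotheses: (1.960 + 0.842)² × 2 × 0.55 × 0.45 / 0.30² = 43.2, so 44; 44 / 0.9 = 48.9, so 49. The more usual formula gives 42, or 47 after dropout. The sample size is not in question here.

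**3. Inflation per arm.** Let k be the share of an arm rescued in weeks 44-48 and still on study drug, m the mean imputed remission probability, and t their true remission probability. The arm's rate is off by k × (m − t), which is k × m if t = 0. Both k and m are assumptions.

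- k = 2 % (1.2 of 60 patients), m = 10-30 %: 0.2 to 0.6 points.
- k = 10 % (6 of 60), m = 50-70 %: 5 to 7 points.

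**4. Effect on the difference (arm 1 minus arm 2), with m = 70 % and 40 %.**

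- k = 5 % and 5 %: 3.5 − 2.0 = +1.5 points.
- k = 10 % and 5 %: 7.0 − 2.0 = +5.0 points.
- k = 3 % and 10 %: 2.1 − 4.0 = −1.9 points.

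**5. Cross-check.** Take 70 % and 40 % as the true rates with rescued patients counted as not in remission. Assessed patients then remit at p / (1 − k). Imputing at that rate gives p + k × p / (1 − k) = p / (1 − k).

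| k arm 1 / arm 2 | Estimated rates | Difference |
|---|---|---|
| 0 / 0 | 70.0 / 40.0 % | 30.0 |
| 0 / 10 % | 70.0 / 44.4 % | 25.6 |
| 5 / 15 % | 73.7 / 47.1 % | 26.6 |
| 10 / 10 % | 77.8 / 44.4 % | 33.3 |
| 10 / 5 % | 77.8 / 42.1 % | 35.7 |

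Imputing at half the assessed patients' rate shrinks the shift: 10 % / 10 % gives 31.7 points and 5 % / 15 % gives 28.3.

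**The case against.** **Reach is narrow.** The rescue sentence refers to waiting for the week 12, 24 and 36 time points, so it mainly describes bridging to those visits. No visit is scheduled between weeks 36 and 48 except the week-28-type safety visits that fall earlier, so late rescue needs an unscheduled contact, and the protocol presents steroid in the window as something unavoidable. This stands: the number affected may be one or two per arm. But the sentence permits rescue up to week 48, and one patient in 60 is 1.7 points.

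**The imputation is not blind.** Only the joint assessment is cancelled. ESR and patient VAS are separate rows in Table 3 at week 48, and the week-36 DAS28 exists. Whether these enter the model is a matter for the separate SAP, which is not shown. This largely stands, and it makes the high values of m less plausible. Two limits remain. Recent steroid can itself lower ESR and VAS. And no patient rescued in the window has an observed week-48 joint count, so the model must borrow from patients who were not rescued. A good model lowers m but does not bring it to zero.

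**Sensitivity analyses are planned.** The worst-case and missing-not-at-random analyses would show the dependence. They leave the primary estimate unchanged, and complete-case analysis simply drops these patients.

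**Stronger readings.** A reader might infer that the primary result is materially biased, or biased towards etanercept. The documents give no rescue frequency, and the direction depends on which arm has more late rescue. A reader might also infer that these patients are known not to be in remission at week 48. Active disease at rescue, up to four weeks earlier, does not prove DAS28 of 2.6 or more at the visit. Finally, one might conclude that the joint assessment should go ahead regardless of steroid. That would undo a deliberate guard against steroid masking and is not needed.

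**Conclusion.** The point holds in a limited form. As written, the plan sends patients rescued for active RA in weeks 44-48, and still on study drug, to missing-at-random imputation of the primary outcome, and some will be counted as remitters. The handling follows from rules the protocol itself fixes; only the imputation model is left open.

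The size is unknown. It is below 1 point per arm if late rescue is rare and the model is informative, and several points if late rescue reaches 10 % and imputed remission 50-70 %. In the cross-check, a 30-point difference moved to between about 26 and 36. All of this rests on assumed k and m and on t = 0. Should-fix: the change is cheap and extends logic the plan already uses.

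**What to change.** In Missing data, extend the non-responder rule: a patient whose week-48 joint assessment is not performed because of rescue corticosteroid for active RA is counted as not in remission in the primary analysis.

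As a sensitivity analysis, multiply impute these patients with rescue, week-36 DAS28, and week-48 ESR and VAS in the model. Rescue should be coded so that it can be estimated, for example as any rescue during the trial, because an in-window indicator has no observed week-48 joint counts behind it.

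Keep multiple imputation for assessments missed because of steroid given for a non-RA indication, where missing at random is more plausible, and for other missing data. The rescue rule and the assessment window need not change. If the SAP already contains such a rule, the protocol wording only has to be brought into line with it.

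Cost: one sentence in the protocol, matched in the SAP, and the reason for each missed assessment recorded. Remission rates will be slightly lower, and a few rescued patients who might truly have been in remission at week 48 will count as failures. The sensitivity analysis shows how much that matters.
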